# **0. Study Overview**

| Study Title | | Intraoperative cell-salvaged versus allogeneic red blood cell transfusions in high-bleeding-risk cardiovascular surgery: Protocol for a single-center, randomized, parallel-group, noninferiority trial |
| --- | --- | --- |
| Principal Investigator | | [name] |
| Study Objective | | The objective of this study is to evaluate, through a single-blind randomized controlled non-inferiority trial, the hypothesis that transfusing intraoperative cell salvage blood for anemia after CPB in high-risk bleeding cardiovascular surgery does not result in greater blood loss in the ICU compared to transfusing only allogeneic RBC, without using cell salvage blood. |
| Study Design | | Single-blind, randomized, parallel-group, non-inferiority trial |
| Study Participants | | Patients undergoing cardiovascular surgery with CPB |
| Eligibility Criteria | Inclusion Criteria | <Provisional registration>   1. Patients who have given informed consent. 2. Patients aged 40 years or older at the time of consent acquisition. 3. Patients scheduled to undergo elective cardiovascular surgery using CPB with a median sternotomy approach. 4. Patients meeting any of the following conditions (high bleeding risk cases):   (a) Re-operative chest surgery following a prior median sternotomy approach.  (b) Patients undergoing surgery involving the aortic root (Ross procedure, aortic valve replacement with annular enlargement, aortic root replacement), ascending aorta replacement, or arch aorta replacement.  (c) Patients undergoing surgery for two or more valve diseases, excluding tricuspid annuloplasty.  (d) Patients undergoing CABG combined with valve surgery, excluding tricuspid annuloplasty.  <Final registration>  Patients who have received allogeneic blood transfusion during CPB. |
|  | Exclusion Criteria | <Provisional registration>   1. Patients scheduled for descending aorta replacement, thoracoabdominal aorta replacement, heart transplantation, ventricular assist device implantation, or pulmonary valve replacement. 2. Patients with an extremely high risk of bleeding. 3. Patients who have not adhered to the prescribed withdrawal periods for antiplatelet or anticoagulant medications. 4. Patients with active bacterial or viral infections. 5. Pregnant or breastfeeding patients. 6. RhD negative patients. 7. Patients with positive irregular antibodies. 8. Other patients deemed unsuitable for participation by the principal investigator or study team.   <Final registration>   1. Patients who fail to adhere to the prescribed withdrawal periods for antiplatelet or anticoagulant medications after pre-registration and before the surgery date. 2. If the surgical procedure is changed between pre-registration and the surgery date, or during the surgery, and it conflicts with the pre-registration inclusion criteria or meets any of the pre-registration exclusion criteria. |
| Investigational Product | Intervention group | Intraoperative cell salvage blood will be used preferentially over allogeneic RBC products for anemia after CPB. If anemia is not corrected by cell salvage blood, or if it is anticipated to remain uncorrected, allogeneic RBC will be transfused. |
|  | Control group | Allogeneic RBC will be transfused for anemia after CPB, without the use of intraoperative cell salvage. |
| Overview of Study Procedure | | Informed consent and pre-registration will be obtained prior to surgery, and post-registration will occur during the surgery. After registration, participants will be randomly assigned in a 1:1 ratio to either the cell salvage group or the allogeneic RBC transfusion group. The randomization will use stratified block randomization. Throughout the study period, blinding will be maintained for the participants, evaluators, surgeons, surgical assistants, and the physicians involved in postoperative management. The investigational product will be administered when anemia with a hemoglobin level below 10.0g/dL is confirmed or anticipated based on laboratory tests. |
| Duration of Intervention | | The investigational product will be administered from the time of CPB weaning until the patient exits the operating room. |
| Outcome | Primary outcome | Total drainage volume within 12 hours of ICU admission |
|  | Secondary outcome | 1. The volume of allogeneic RBC transfused from the start of general anesthesia to 12 hours after ICU admission 2. The incidence of re-sternotomy or re-operation for blood clot removal within 48 hours of ICU admission 3. The proportion of patients with total drainage volume exceeding 1000mL within 12 hours of ICU admission |
|  | Safety outcome | 1. Prevalence of any of the following infections: surgical site infection, mediastinitis, urinary tract infection, respiratory infection, central nervous system infection, gastrointestinal system infection, skin and soft tissue infection, or other infection 2. Prevalence of gross hematuria upon ICU admission 3. Prevalence of acute kidney injury within 7 days after surgery, defined in accordance with the Kidney Disease: Improving Global Outcomes criteria. |
| Planned Sample Size | | 142 cases (71 in the intraoperative cell salvage group and 71 in the allogeneic RBC group). |
| Rationale for Sample Size | | Based on preliminary data from patients meeting the eligibility criteria, the average drainage volume within 12 hours of ICU admission for 59 cases using only allogeneic RBC was 674 mL with a standard deviation of 400 mL. Using a non-inferiority margin of 200 mL and power calculations (α = 0.025, β = 0.2), the required sample size was calculated as 128 (64 per group). Accounting for a 10% dropout rate, the final sample size was set at 142 (71 per group). |
| Planned Study Period | | Study Duration: Research approval date – March 31, 2030Enrollment Period: Research approval date – September 30, 2026Follow-up Period: Research approval date – November 4, 2026 |
| Study Secretariat | | National Cerebral and Cardiovascular Center, Department of Transfusion Address: [name], JapanTEL: [contact] ([name])[contact]e-mail：[contact] |

Patients scheduled for elective cardiovascular surgery using CPB with high bleeding risk

Informed Consent

Eligibility Confirmation and provisional registration

Allogeneic RBC Transfusion during CPB

Not Transfused

Transfused

Not registerd

Final registration and randomization

Salvaged RBC group

Administration of salvaged RBC prioritized over allogeneic RBC from weaning of CPB until the patient exits the operating room

　Allogeneic blood group

Only allogeneic RBC transfusion from weaning of CPB until the patient exits the the operating room

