## **Secondary Outcomes**

1. Allogeneic RBC transfusion volume during surgery and for 12 hours from the end of surgery
2. Prevalence of re-thoracotomy within 48hours from the end of surgery
3. Prevalence of the postoperative chest tube blood loss within 12 hours from the end of surgery ≥1000mL

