## **Criterias of choice**

Patients who underwent allogeneic RBC transfusion in a heart-lung machine

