## **Administration of the Study Treatment**

Consent and provisional registration are completed before the day of surgery. The final registration and randomization occurs during CPB. From the point of CPB weaning (protamine administration), the study product is administered based on the hemoglobin levels.

< Administration criteria for the study treatment>

If hemoglobin is less than 10.0 g/dL or is anticipated to drop below this level, transfusion is administered per group assignment.

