## **Visit 3. During Study Treatment**

The following information is collected after weaning from CPB on the day of surgery (allowable range: +3 days). Data isobtained from the anesthesia records (ORSYS) and electronic medical records (MegaOak).

| 1) Study Treatment Information | |
| --- | --- |
| Treatment Information | - Volume of salvaged RBC and transfused allogeneic RBC (a) during from the start of general anesthesia to weaning from CPB, and (b) from weaning from CPB to leaving the operating room - Intraoperative blood loss - Heparin concentration in salvaged RBC (salvaged RBC group only)^*3^ |
| 2) Clinical and Laboratory Data |  |
| Vital signs | Blood pressure, heart rate, peripheral oxygen saturation (SpO₂), central venous pressure, pulmonary artery pressure, cardiac output (at the end of surgery) |
| Physical findings | Gross hematuria upon ICU admission |
| Blood gas analysis | Hemoglobin (at the following time points: after induction of general anesthesia, before initiation of CPB, during CPB, after CPB following protamine administration, and additionally as needed) |
| Laboratory tests | Hemoglobin, platelet count, PT-INR, APTT, fibrinogen, and blood viscoelastic testing (at the following time points: before and after weaning from CPB following protamine administration, at ICU admission, and additionally as needed)  Total protein, albumin, total bilirubin, direct bilirubin, AST ALT, creatinine, LDH, CK, CK-MB, sodium, potassium, chloride, calcium, and CRP (laboratory data collected at the time of ICU and subsequently as required). |
| 2) Concomitant Treatment Information | |
| Concomitant Therapy | - Volume of transfused FFP, platelet concentrates, and cryoprecipitate during (a) from the start of general anesthesia to weaning from CPB, and (b) from weaning from CPB to leaving the operating room - Total intraoperative doses of colloid solutions, tranexamic acid, heparin (excluding that used in the salvage system), and protamine |
| 3) Surgical Information | |
| Surgical Information | Definitive diagnosis, definitive surgical procedure, operative time, CPB time, aortic cross-clamp time, lowest temperature during CPB |
| 4) Adverse Events | |
| AEs | Date of onset, event name, known/unknown, seriousness, severity, causal relationship, treatment, outcome, date of outcome confirmation, other details |

*3 Measured for research purposes

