## **Overall Assessment of Benefits and Burdens to Study Participants**

### **Benefits to participants and potential benefits of the study**

If this study demonstrates that the use of salvaged RBC during cardiovascular surgery does not increase postoperative bleeding, it may support the effective use of salvaged RBC that would otherwise be discarded and reduce the volume of allogeneic RBC transfusions. However, it is unlikely that the participants receives direct medical benefits during the study period.

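### Secondary outcome 1 counts allogeneic RBC given before randomisation, which every randomised patient must have had; unless adjusted for, this costs precision, though it causes no bias

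*Protocol*

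**What the plan says.** The Protocol defines secondary outcome 1 twice. The Study Overview has "The volume of allogeneic RBC transfused from the start of general anesthesia to 12 hours after ICU admission"; the Secondary Outcomes section has "Allogeneic RBC transfusion volume during surgery and for 12 hours from the end of surgery". Both windows open before randomisation.

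Final registration comes immediately before randomisation. Its inclusion criterion is "Patients who have received allogeneic blood transfusion during CPB" in the Study Overview and "Patients who underwent allogeneic RBC transfusion in a heart-lung machine" in the body. The body and the flow chart both specify RBC.

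On timing, the section on administering the study treatment says "The final registration and randomization occurs during CPB". The arms differ only afterwards: "The investigational product will be administered from the time of CPB weaning until the patient exits the operating room".

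Visit 3 collects the operative RBC volumes in two periods: "a) during from the start of general anesthesia to weaning from CPB, and (b) from weaning from CPB to leaving the operating room". Neither outcome definition uses this split.

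The section on benefits says the trial may help "reduce the volume of allogeneic RBC transfusions", and the section on the validity of the trial names the same saving. Secondary outcome 1 is the listed outcome that measures it.

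**The concern.** An outcome meant to show what a treatment changed would normally start when the treatment could first act. Here it starts earlier, and the eligibility rule guarantees that the earlier stretch contains some allogeneic RBC in every randomised patient.

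Two things follow if the total is compared without adjustment. First, chance differences between arms in RBC given before allocation pass straight into the estimate. Second, a percentage reduction is computed on a base that includes blood the treatment could not have saved.

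The stakes are those of a secondary outcome. The primary comparison asks only whether drainage is not worse. The reason to want that result is the saving in donor blood, and the sample size was set for drainage alone, with no power stated for RBC volume.

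**Working it through.** **The plan's own figure.** The only sample size in the Protocol is for drainage: SD 400 mL, margin 200 mL, one-sided α 0.025, power 80%. The normal formula gives 2 × (1.960 + 0.842)² × 400² / 200² = 62.8, so 63 per group. The t-based version gives 64 (power 0.801), as stated. With 10% dropout, 128 / 0.9 = 142.2, against 142 stated. This point does not touch these figures.

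**Inputs for RBC volume.** The documents give none. Let s be the SD of pre-randomisation volume divided by the SD of post-randomisation volume, and r their correlation, the same in both arms. Set the post-randomisation variance to 1. The values of s and r below are assumptions.

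**Expected difference.** Total = pre + post. Randomisation makes the expected difference in pre zero, so the expected difference in the total equals that in post. There is no bias.

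**Variances.**
- Total, unadjusted: 1 + s² + 2rs
- Post, unadjusted: 1
- Post, linearly adjusted for pre: 1 − r²

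The total minus adjusted post is s² + 2rs + r² = (s + r)², which is never negative. It is zero only when r = −s. The one degree of freedom spent on the covariate is negligible with about 128 patients.

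The first ratio below is the effect of the window alone. The second also contains the ordinary gain from covariate adjustment. The power column takes an effect with 80% power on unadjusted post volume (two-sided 0.05, 1:1) and shows the power left when the unadjusted total is used.

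| s | r | Total ÷ post unadjusted | Total ÷ post adjusted | Power on total |
|---|---|---|---|---|
| 0.25 | 0 | 1.06 | 1.06 | 78% |
| 0.5 | −0.3 | 0.95 | 0.95/0.91 = 1.04 | 82% |
| 0.5 | 0 | 1.25 | 1.25 | 71% |
| 0.5 | 0.3 | 1.55 | 1.55/0.91 = 1.70 | 61% |
| 0.5 | 0.5 | 1.75 | 1.75/0.75 = 2.33 | 56% |
| 1 | 0 | 2.00 | 2.00 | 51% |
| 1 | 0.3 | 2.60 | 2.60/0.91 = 2.86 | 41% |
| 1 | 0.5 | 3.00 | 3.00/0.75 = 4.00 | 37% |

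Interval widths scale with the square root. For the window alone they are √1.25 = 1.12 to √1.75 = 1.32 times wider at s = 0.5 with r from 0 to 0.5, and √2 = 1.41 to √3 = 1.73 times wider at s = 1. The window alone adds no variance when r ≤ −s/2.

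**Relative reduction.** If pre-randomisation RBC is a share p of the control-arm mean total, a relative reduction on post volume shrinks by the factor (1 − p) when expressed on the total. The documents give no p.

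**Equivalence of the two remedies.** Since total = pre + post, regressing the total on arm and pre gives the same treatment estimate and standard error as regressing post on arm and pre. Only the coefficient of pre changes, by 1.

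**The case against.** The strongest reply is that the total is a coherent outcome: it is the donor blood a patient receives around the operation, and it is unbiased. If the analysis adjusts the total for the earlier volume, no precision is lost. The Protocol leaves the analysis to a separate SAP, which was not available here, and it nowhere says that the comparison will be unadjusted.

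Much of this stands. The loss belongs to an unadjusted comparison of the total, and an SAP could remove it. But the window itself is fixed in the Protocol, in both definitions, and the covariate that would repair it is not among the listed data. Visit 3 cuts at weaning, while randomisation happens earlier, during bypass. The pre-weaning volume may therefore include RBC given after allocation, when the anaesthesiologist already knows the arm.

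It is also fair that the loss may be small. Transfusion is triggered by a haemoglobin threshold, so more RBC on bypass could mean less needed later. A negative r is plausible, and the window alone can then cost nothing against unadjusted post volume. It still cannot beat the adjusted analysis.

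A reader might infer that the pre-randomisation part is a large share of each value. The documents give no RBC volume on bypass and set no minimum for eligibility, so this is unsupported. Nor can the fourfold variance be laid to the window: at s = 1, r = 0.5 the window accounts for a factor of 3.0, and the rest is the usual gain from adjustment.

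**Conclusion.** The point holds as a matter of efficiency. As defined, secondary outcome 1 includes RBC that allocation cannot have affected, in every randomised patient. An unadjusted comparison of it is never more precise than post-randomisation volume adjusted for the earlier volume. The size depends entirely on the assumed s and r: the window alone changes the variance by a factor from 0.95 to 3.0 over the values shown, and the comparison with the adjusted analysis runs from 1.04 to 4.0.

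A reader might take this as bias in the RBC comparison, or as a threat to the non-inferiority conclusion. Neither follows: the expected difference is unchanged, and the drainage outcome and its sample size are unaffected. Nor does the Protocol label this outcome as key. It is the first of three secondary outcomes, and its importance rests on the stated aim of saving donor blood. The change is worth making because it costs little and cannot reduce precision beyond one degree of freedom.

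**What to change.** Define secondary outcome 1 as allogeneic RBC volume from randomisation to 12 hours after ICU admission, and analyse it with the volume given before randomisation as a covariate. Equivalently, keep the total as the outcome and prespecify adjustment for that volume. Report the whole-period total descriptively, so that overall donor exposure remains visible.

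Add one field, taken from the anaesthesia record: allogeneic RBC volume from the start of anaesthesia to the time of randomisation. The volume up to weaning should not stand in for it without a check that no RBC was given between allocation and weaning.

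The cost is a sentence in each of the two outcome definitions, a matching line in the SAP and the one field. No treatment rule, eligibility criterion or sample size changes.

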**Observation Period**: **30days**

The primary outcome will be the measurement of the total drainage volume within 12 hours of ICU admission. As a secondary outcome, patients will be followed for 30 days after the administration of the investigational treatment.

Abbreviations

| AE | Adverse event |
| --- | --- |
| ACT | Activated clotting time |
| ALT | Alanine aminotransferase |
| APTT | Activated partial thromboplastin time |
| AST | Aspartate aminotransferase |
| ATIII | Anti thrombin III |
| BNP | Brain natriuretic peptide |
| CABG | Coronary artery bypass grafting |
| CDC | Centers for disease control and prevention |
| CK | Creatine kinase |
| CPB | Cardiopulmonary bypas |
| CRF | Case report forms |
| CRP | C-reactive protein |
| FAS | Full analysis set |
| FBS | Fast blood sugar |
| FDP | Fibrin/fibrinogen degradation products |
| FFP | Fresh frozen plasma |
| ICU | Intensive care unit |
| ITT | Intent-to-treat population |
| LDH | Lactate dehydrogenase |
| PPS | Per protocol set |
| PT-INR | Prothrombin time-international normalized ratio |
| RBC | Red blood cell |
| SAE | Serious adverse event |
| SSI | Surgical site infection |

# **Background and rationale**

## **Current Status of the Target Disease in Japan and Abroad**

In Japan, an aging population and declining birthrate are expected to result in decreased blood donations and an increased demand for blood products. It is estimated that there will be a shortfall of approximately 330,000–650,000 blood donations by 2025. [1] Therefore, reducing the use of blood products is an urgent issue.

Over 70,000 cardiovascular surgeries are performed annually in Japan. [2] Among medical specialties, cardiovascular surgery ranks second after hematology in the use of RBC and platelets and first in the use of FFP. [3] Reducing blood transfusion volumes in major cardiovascular surgeries is a major challenge.

## **History and Overview of Standard Treatments**

The standard method for rapidly correcting anemia during major cardiovascular surgery is allogeneic RBC transfusion.

## **Current Standard Treatments and Outcomes**

Although screening for known viruses has reduced the incidence of infection from allogeneic RBC transfusions, the risk of transmission of unknown viruses remains a concern. Furthermore, studies have reported that allogeneic RBC transfusions are associated with a higher risk of surgical site **infections**[4], **pneumonia**[5], and **renal dysfunction**[6] after major cardiovascular surgeries.

In CABG, the use of allogeneic RBC is associated with an increased risk of mortality, with a reported risk ratio of 1.7 (95% confidence interval: 1.4–2.0).[7]

## **Challenges and Uncertainties in the Current Standard Treatment Leading to the Necessity of This Clinical Trial**

One approach to avoid the issues associated with allogeneic RBC transfusions is autologous blood transfusion. There are three methods of autologous blood transfusion: pre-donation (or blood banking), dilutional, and cell salvage transfusion. Among these, cell salvage is commonly used in major cardiovascular surgery.

In cell salvage, a specialized device is used to collect blood lost during surgery from the surgical field. The collected blood is passed through a filter in a reservoir to remove foreign matter and stored. Once a certain amount of blood has been collected, it is concentrated and washed, and then stored in a blood bag to be returned to the patient.

In heart and large vessel surgeries, where blood loss tends to be relatively high, blood recovery offers the advantage of reducing the need for allogeneic RBC transfusion, helping decrease the risks associated with donor blood transfusions.[8-11]。A systematic review and meta-analysis published by Cochrane in 2023 reported that the use of blood recovery during heart surgery with CPB resulted in a reduction of 1.47 units of allogeneic RBC transfusion (95% confidence interval: 0.36-2.59).[12] A facility in Japan, which performed approximately 1,100 cases of cardiac and vascular surgery over a 3-year period, reported that 78% of these cases involved blood recovery. As a result, a total of 9,301 units of allogeneic RBC transfusion were reduced over the 3 years.[13] Overseas guidelines recommend the use of blood recovery during cardiac surgery involving CPB.[14, 15]

However, there are reports that administering large amounts of salvaged RBC can cause coagulopathy due to residual heparin that was not completely removed during the washing process.[11] In a systematic review and meta-analysis by Cochrane, which reported a reduction in the use of allogeneic RBC transfusions with the use of salvaged RBC, the study population largely consisted of procedures with low blood loss risks, where transfusions were often not required. Therefore, the issue of residual heparin in salvaged RBC causing complications after the antagonism of heparin, particularly in high-risk surgical procedures that require relatively large amounts of transfusions, remains unresolved. Specifically, whether salvaged RBC can be used without increasing bleeding after separation from CPB remains unclear. According to a survey conducted among major facilities in Japan performing cardiovascular surgery, 40% of the cases had salvaged RBC prepared but discarded without being used. Therefore, it is urgent to to investigate the impact of salvaged RBC transfusions on blood loss in patients with a high risk of bleeding.

